#### Strategies to improve adherence to interventions {11c}

NA—Compliance with medication is not applicable as administration of both IMPs are performed within a clinical setting by the treating investigator.

#### Relevant concomitant care permitted or prohibited during the trial {11d}

N/A—There are no additional needs or prohibitions for the purposes of this trial once patient fits inclusion criteria.

#### Provisions for post-trial care {30}

The Rotunda Hospital (sponsor) will indemnify claims from participants for injury caused by their participation in the clinical trial*.* However, as this clinical trial is being carried out at a hospital site, the hospital will continue to have a duty of care to the participants of the clinical trial.

There will be no arrangements to provide the IMPs to trial participants post trial as this study is specific to IOL.

#### Outcomes {12}

For all study participants, information will be recorded in the electronic chart as is standard for all patients in the hospital. Data on all of the above primary and secondary objectives will be collected and collated.

At the initiation of induction, the gestational age and exact time of initiation of induction will be recorded.

A questionnaire and stamped addressed envelope will be sent to participants to complete following delivery, in order to assess their satisfaction scores with the process of outpatient induction.

##### Secondary outcome measures

Overall change in Bishop score before and after cervical ripeningRates of vaginal delivery at 36 h after insertion of either Propess or Dilapan-S®Rates of vaginal delivery at 48 h after insertion of either Propess or Dilapan-S®The need for second induction modalityRates of hyper-stimulation*Rate of failed inductionOverall length of stay in hospitalRates of adverse neonatal outcomeRates of adverse maternal outcomesMaternal satisfaction scores with the outpatient induction processCaesarean delivery rates, categorised by “overall rate”, “rate for failure to progress/failed induction”, and “rate for non-reassuring fetal testing”Analgesia use in each group, including rates of epiduralCompare rates of 39 weeks’ successful vaginal delivery in the outpatient setting to rates of successful vaginal delivery in the inpatient setting**.

*Defined as more than 7 contractions in a 15-min time period persistently for more than 30 min and requiring a medical intervention (such as a clinical decision to remove the Propess/Dilapan or administer a medication such as Terbutaline)

**Defined as a group of low-risk nulliparous women who did not undertake elective induction of labour at 39 weeks as part of this trial

The primary objectives will therefore assess the efficacy of achieving labour with each of the study induction methods. The secondary objectives will assess other efficacy measures, safety measures and maternal satisfaction scores which are important factors in deciding whether this is a feasible option long term, and risk stratification in this process. Although many studies have shown both induction mediums to be low risk, it is important to compare the outcomes as above in order to guide the best possible IOL methods and create the most appropriate protocol for women to undergo IOL.

#### Participant timeline {13}

The participant timeline is shown in Fig. 1.

**Fig. 1 Fig1:**
[figure not shown]
Schedule of assessments timeline for HOME IND trial

#### Sample size {14}

A single primary comparison will be used to determine efficacy. The sample size was therefore revised, from a potentially under-powered study of two co-primary comparisons, to an adequately powered study of a single primary comparison.

A 10% margin was used as the non-inferiority margin for the treatment comparison of Dilapan-S (combined groups) versus Propess. SVD rates were assumed to be 70%, 75%, and 80% in the Propess, Dilapan-S® (24 h), and Dilapan-S® (12 h) groups, respectively. Assuming 90% statistical power, a one-sided 2.5% level of statistical significance, and equal treatment group allocation, the study sample size required is 285 for a per-protocol analysis. Allowing for a 15% non-adherence rate, the total required recruitment is 327 (109 per group) for the intention-to-treat analysis. Other treatment comparisons will be considered secondary and exploratory.

#### Recruitment {15}

This trial will be conducted at one hospital site. Identification of potential subjects will be from the antenatal clinic lists. Potential participants who may wish to enquire about the study through advertising will also be able to contact the investigator.

There are approximately 3000 eligible patients per year attending the Rotunda as published annually in the hospital reports. Similar trials in the past have shown an uptake rate of 30% for inpatient induction of labour. With a more conservative uptake rate of about 20% (3000 × 20% = 600), we would therefore expect to recruit the required number of participants within 30 months (recruitment will have a maximum allowable duration of 30 months), allowing for dropout rates and those that fit exclusion criteria.

### Assignment of interventions: allocation

#### Sequence generation {16a}

Patients will be randomised using simple random allocation to either Dilapan-S® (12-h insertion or 24-h insertion) or Propess in a 1:1:1 ratio using a block size of 6 via a computer-generated randomisation procedure (software SAS Version 6.4).

#### Concealment mechanism {16b}

The use of a validated password website by the pharmacy department, not the investigator, will ensure concealment.

#### Implementation {16c}

A computer-generated randomisation sheet will be used to assign study participants to either Propess, Dilapan-S® 12 h, or Dilapan-S® 24 h groups at visit 1. The randomisation sheet will provide notification of the treatment package to be assigned to the participant and a log of each randomisation will be retained. The randomisation will be performed by the pharmacy department and relayed to the investigator. Subsequent to screening and consent procedures, the participants will be randomised to one of the three groups. The randomisation will use a block size of 4, and the random number seed-generator and generating program will be retained for reproducibility. The software SAS 6.4 will be used to generate the randomisation list.

### Assignment of interventions: blinding

#### Who will be blinded {17a}

N/A—This is an open-label trial; therefore, there will be no blinding of investigators, medical staff, or statisticians on this trial.

#### Procedure for unblinding if needed {17b}

N/A—This design is open label; therefore, unblinding will not occur.

### Data collection and management

#### Plans for assessment and collection of outcomes {18a}

Data will be entered prospectively at the time of the visits into the patient’s electronic chart (source data) as is standard protocol within the hospital. All data will be collected by a member of the team from the electronic chart or filled questionnaires and entered into the *electronic case report form (eCRF)*.

Source data are all information, original records of clinical findings, observations, or other activities in a clinical trial necessary for the reconstruction and evaluation of the trial.

For data where no prior record exists and which are recorded directly in the eCRF, the eCRF will be considered the source document, unless otherwise indicated by the investigator.

In addition to the above, date(s) of conducting informed consent, trial number, study arm, and the fact that the patient is participating in a clinical trial *will* be added to the patients’ medical record contemporaneously.

It will be the responsibility of the investigator to ensure the accuracy of all data entered in the CRFs. The delegation log will identify all those personnel with responsibilities for data collection and handling, including those who have access to the trial database.

#### Plans to promote participant retention and complete follow-up {18b}

N/A—The IMP is given by the investigator at time of induction; therefore, no deviation is possible.

#### Data management {19}

Data handling will be in accordance with Data Protection Legislation. The study coordinator will be the data controller and will ensure data security, privacy (anonymisation), and archival, in accordance with the Hospital IT department data handling policies. The study data will be stored in a centralised and secured area and will not be distributed to a third party. The study data will only be accessed by study personnel, as required, for data monitoring and data analysis.

The software STATA 16 ICE will be used for data entry using pre-specified fields. In addition, the SAS Version 9.4 software will be used for querying data (anomaly detection and rectification), for DSMB reporting and for statistical analysis at study completion. A detailed Statistical Analysis Plan (SAP) will be finalised prior to last-patient last-visit.

#### Confidentiality {27}

All data will be handled in accordance with the applicable Data Protection legislation.

The case report forms (CRFs) will not bear the subject’s name or other personal identifiable data. The subject date of birth and trial identification number will be used for identification.

#### Plans for collection, laboratory evaluation, and storage of biological specimens for genetic or molecular analysis in this trial/future use {33}

N/A—No such specimens are collected in this trial.

### Statistical methods

#### Statistical methods for primary and secondary outcomes {20a}

The analysis of the primary outcome will use a confidence interval (95% level of confidence) for simple differences in proportions. Non-inferiority will be determined on the lower confidence interval limit (equivalent to a one-sided 97.5% confidence interval). Conditional on non-inferiority being demonstrated, superiority will be determined. The analyses will be performed in the per-protocol population, supported by an intention-to-treat analysis.

Secondary outcomes will be compared using confidence intervals and hypothesis tests. However, these will be considered exploratory in nature. No adjustment for multiple testing will be performed.

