Visit 3: Reassessment. Patients will return to hospital at the allocated time, or before if clinically necessary (e.g. spontaneous rupture of membranes, vaginal bleeding, concerns re fetal movements or regular contractions). Vital signs will be measured, and urinalysis will be performed. A CTG will be performed. The IMP will be removed as per manufacturer’s guidelines, and reassessment of the cervix will be performed, and Bishop score will be determined. Clinical staff will assess whether the patient is suitable for artificial rupture of the membranes (ARM) or whether further ripening is needed. If further ripening is needed, Prostin gel at the dose of 1 mg will be given, a CTG will be performed, and the patient will be reassessed approximately 6 h thereafter. If deemed suitable for ARM, the patient will undergo same, a CTG will be performed, and the patient will be transferred to the labour ward when space is available. If required, oxytocin will be used to induce or augment labour as per hospital guidelines.

Visit 3 assessments will include:Vital signsBishop scorePhysical examination (if symptom driven)Abdominal examinationAdverse event reviewConcomitant medication reviewCTG

Visit 4: Delivery visit. Data is recorded from the electronic chart as per the schedule of events. Following delivery, a Maternal Satisfaction Questionnaire and stamped addressed envelope are sent to all participants to assess their experience throughout the trial.

Visit 4 assessments will include:Vital signsPhysical examination (if symptom driven)Delivery detailsMaternal Satisfaction QuestionnaireNeonatal outcomesAdverse event reviewConcomitant medication review

Visit 5: Six weeks following delivery, the participants are contacted, and data is recorded as per the schedule of events. This concludes the patient’s participation in the trial.

Visit 5 assessments will include:Maternal Satisfaction Questionnaire *(if unable to complete at visit 4)*Neonatal outcomes (if there has been a change since visit 4)Adverse event reviewConcomitant medication review

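### The superiority test is assigned to the per-protocol set, and non-inferiority can be claimed on that set without ITT agreeing

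*Protocol article*

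**What the plan says.** Statistical methods for primary and secondary outcomes {20a} takes three steps in order. Non-inferiority is read from the lower limit of a 95% interval for a difference in proportions. Next comes: "Conditional on non-inferiority being demonstrated, superiority will be determined". The closing sentence names the analysis set: "The analyses will be performed in the per-protocol population, supported by an intention-to-treat analysis". The plural follows both tests. No other section moves superiority to ITT or makes a non-inferiority claim depend on ITT.

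Sample size {14} is built the same way. It states: "A 10% margin was used as the non-inferiority margin for the treatment comparison of Dilapan-S (combined groups) versus Propess". It requires 285 women for the per-protocol analysis and, after a 15% allowance for non-adherence, recruits 327 (109 per group) for ITT. Plans to promote participant retention and complete follow-up {18b} says instead that the investigator gives the product and "therefore, no deviation is possible".

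**The concern.** A superiority claim is protected by comparing the groups as randomised. A per-protocol set is formed by events after randomisation, so a difference found in it may reflect who was removed. ITT is the usual conservative set for superiority; per-protocol is not.

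The article documents several routes by which women can drop out of such a set while allocation is known:

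- Randomisation is at visit 1, women are told their group before the induction date, and all eligibility criteria are checked again at visit 2 (Intervention description {11a}).
- Women may be withdrawn as unsuitable for outpatient care, or because going home is judged unsafe after induction has begun (Criteria for discontinuing or modifying allocated interventions {11b}). The second judgement could depend on how the device is acting.
- Investigators, medical staff and statisticians are all unblinded (Who will be blinded {17a}).
- COVID-19 infection at visit 2 has already left some randomised women untreated (Discussion).

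For non-inferiority, showing a per-protocol analysis is normal practice, since ITT can dilute a true difference. The weakness is that it decides alone: the text gives no rule for what follows if ITT misses the margin. What is at stake is the trial's headline claim.

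**Working it through.** **Inputs.** From {14}: vaginal delivery rates of 0.70 (Propess), 0.75 (Dilapan-S 24 h) and 0.80 (Dilapan-S 12 h); margin 0.10; one-sided 2.5%; 90% power; equal allocation. Pooling the two Dilapan-S groups gives (0.75 + 0.80)/2 = 0.775 and a 2:1 comparison. Differences are Dilapan-S minus Propess on the success scale.

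**1. The plan's own figure.** For the Propess group, n = (z_α√V0 + z_β√V1)²/d².

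- d = 0.775 − 0.70 + 0.10 = 0.175.
- V1 = 0.70×0.30 + 0.775×0.225/2 = 0.2972.
- V0 uses the Farrington-Manning restricted estimates (about 0.805 and 0.705), giving about 0.2608.
- n = (1.960×0.5107 + 1.2816×0.5452)²/0.0306 = 94.3, so 95, and 95 × 3 = 285. This matches.
- The simpler unpooled formula gives 102 × 3 = 306.
- 285 × 1.15 = 327.75, taken as 3 × 109 = 327.

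The trial was therefore sized with per-protocol as the deciding set.

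**2. What ITT gives at 327 (109 v 218), planned rates.**

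- SE = √(0.21/109 + 0.1744/218) = 0.0522.
- Non-inferiority: Φ(0.175/0.0522 − 1.960) = 91.8%. Exact enumeration of the Wald interval gives 92.7%.
- Superiority: Φ(0.075/0.0522 − 1.960) = 30%. On a per-protocol set of 285 it is about 26% to 27%.
- If 15% of Dilapan-S women did no better than Propess, the combined rate is 0.85×0.775 + 0.15×0.70 = 0.764 and ITT non-inferiority power is 87.7%.

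**3. Cost of requiring both sets.** Losing 15% of 327 leaves about 278, or 93 per group. Enumerated per-protocol non-inferiority power there is 88.2%, so passing both cannot exceed 88.2%. A simulation of 400,000 trials at the planned rates, with 16 women per group dropped at random from 109, gave 87% for passing both. At the planned rates the extra requirement therefore costs about one point relative to per-protocol alone.

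**4. Illustration of selection (assumed, not documented).** Suppose a fraction e of each arm is excluded. Propess exclusions are unrelated to outcome, and excluded Dilapan-S women have success rate s. With true Dilapan-S rate p, the per-protocol rate is (p − e·s)/(1 − e). For p = 0.70, e = 0.15, s = 0.50 it is (0.70 − 0.075)/0.85 = 0.735. With 92.65 v 185.3 women the SE is 0.0576, and the chance of declaring superiority is Φ(0.0353/0.0576 − 1.960) = 8.9%.

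| e | s | False superiority (true 0.70 v 0.70) | False non-inferiority (true 0.60 v 0.70) |
|---|---|---|---|
| 15% | 50% | 8.9% | 4.8% |
| 15% | 40% | 15.1% | 8.6% |
| 15% | 30% | 23.7% | 14.4% |
| 5% | 50% to 30% | 3.9% to 5.8% | 3.1% to 4.7% |

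The nominal rate is 2.5% throughout. If exclusions affect both arms alike the inflation shrinks; if excluded Dilapan-S women do better than average, the bias runs the other way.

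**The case against.** The strongest reply is that per-protocol is conventional for non-inferiority, that non-inferiority is the primary objective, and that an ITT analysis is promised and the recruitment total stated for it. Requiring both sets is a stricter standard, not the correction of a misstatement. This stands in part, and it is why the non-inferiority half is put only as a set that should not decide alone. It does not rescue superiority, where the convention points to ITT.

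It can also be said that the one reported cause of non-receipt, COVID-19 infection before insertion, is probably unrelated to arm, and that 15% is a planning allowance, neither a ceiling nor evidence of selective loss. Both are fair, and they limit what can be said about size.

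A reader might infer more than the documents support:

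- **That early returners would be dropped and bias the contrast by dwell time.** The article makes early return part of the pathway: "Patients will return to hospital at the allocated time, or before if clinically necessary". Nothing calls it non-adherence. A contrast between 24 h and 12 h also does not map onto the primary comparison, since Propess and half of the pooled Dilapan-S women are in 24 h arms.
- **That the missing per-protocol definition is a fault, or that unblinded staff will choose the set.** The article does not say who assigns women to it, and a detailed SAP, not shown, is promised in Data management {19}.
- **That the plan lets a per-protocol claim stand against a failed ITT result.** The text has no rule for disagreement; it simply does not prevent this.
- **That a shift of particular size is expected.** No outcome rates for excluded women are given.

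**Conclusion.** The point holds for both tests, with different force. For superiority, {20a} assigns the wrong deciding set, and this is a stated rule rather than detail left to the SAP. For non-inferiority, the per-protocol analysis is acceptable as one of two required analyses but not as the sole basis.

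The conclusion rests on the plain reading of {20a} and on the documented routes for loss after randomisation. It does not rest on the illustrative error rates, which depend entirely on assumed outcomes in excluded women. Planned superiority power is only about 30% even on ITT, so superiority is a secondary step here. The rule still needs correcting, because it would govern any such claim.

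The statement in {18b} that deviation cannot occur is a separate inconsistency. It conflicts with the 15% allowance in {14} and sits badly with the untreated randomised women reported in the Discussion. It does not itself show that the analysis set is wrong.

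**What to change.** Reword {20a}, and carry the rule into the SAP:

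- Test superiority in the ITT set, meaning all randomised women analysed as allocated.
- Claim non-inferiority only if the lower 95% limit for Dilapan-S (combined) minus Propess exceeds −10 points in both the ITT and the per-protocol sets.
- Reconcile {18b} with the non-adherence allowance in {14}.

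This is a wording change with no added recruitment at the planned rates. The cost is a slightly lower chance of a non-inferiority claim than with either set alone. It requires mode of delivery for women who never received the product or were withdrawn, as far as consent allows; Outcomes {12} says this type of information is charted routinely for all hospital patients. The article has the SAP finalised before the last patient's last visit and recruitment ending around mid-June 2023, so on its own timetable the rule could be fixed before analysis.

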#### Interim analyses {21b}

N/A—No interim analysis will be performed.

#### Methods for additional analyses (e.g. subgroup analyses) {20b}

Multiple (multivariate) logistic regression for the primary endpoints to adjust for potential prognostic variables will be performed. Such analysis will be deemed exploratory in nature and not considered the primary analysis.

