#### Intervention description {11a}

Eligible patients will be prescreened from antenatal clinic lists and contacted to gauge interest in participating. An information leaflet will be sent to any interested parties. If the patient is interested having read the information, a clinic date will be assigned at approximately 38 weeks.

Visit 1: Clinic. The patient will attend a specialised home induction antenatal clinic appointment at approximately 38 weeks’ gestation. They will have vital signs measured and urinalysis carried out. A growth scan and fetal wellbeing scan will be performed by a sub investigator, and eligibility criteria will be assessed. Informed consent will be obtained from patients who meet inclusion criteria and do not meet exclusion criteria. They will then be randomised to one of 3 groups: Dilapan-S 12 h, Dilapan-S 24 h, or Propess 24 h. They will be allocated a date for IOL from 39+0 to 39+4 weeks’ gestation. Patients will be informed of their allocated group in advance of their allocated induction date.

Visit 1: Recruitment. Baseline assessments include:Obtain medical historyVital signsPhysical examination (if symptom driven)Abdominal examinationWeight, height, BMIUrinalysisUltrasoundRandomisation

Visit 2: Induction. Patients will be admitted to the hospital on the assigned induction date and will have vital signs and urinalysis performed. They will undergo a scan to assess biophysical profile. All eligibility criteria will be reassessed before commencement of IOL. Cardiotocograph (CTG) monitoring will be performed for at least 20 min prior to commencing IOL. The cervix will be examined, and Bishop score will be determined. Provided patients are still eligible; IOL will be carried out with the allocated device as per manufacturer’s instructions. CTG monitoring will be performed for 30 min (Dilapan-S) or 60 min (Propess) following application of the relevant intervention. Participants will then go home with a patient safety checklist and instructions for monitoring at home and instructions on when to return to hospital. Two phone calls will be made to the patients whilst at home to assess patient wellbeing.

Visit 2 assessments will include:Vital signsUrinalysisBishop scoreUltrasoundPhysical examination (if symptom driven)Abdominal examinationInvestigational medicinal product (IMP) administrationAdverse event reviewConcomitant medication reviewCTG

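### The non-inferiority decision rests on an unadjusted difference; a standardised risk difference adjusted for age and BMI would add a little precision on the same 10-point scale at almost no cost

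*Protocol article*

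**What the plan says.** The section on statistical methods for primary and secondary outcomes {20a} fixes the deciding analysis: "The analysis of the primary outcome will use a confidence interval (95% level of confidence) for simple differences in proportions". On populations it says: "The analyses will be performed in the per-protocol population, supported by an intention-to-treat analysis".

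The section on additional analyses {20b} adds: "Multiple (multivariate) logistic regression for the primary endpoints to adjust for potential prognostic variables will be performed". It does not name the covariates or the effect measure to be reported, and it ranks the model below the crude comparison: "Such analysis will be deemed exploratory in nature and not considered the primary analysis".

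The margin is set under Sample size {14}: "A 10% margin was used as the non-inferiority margin for the treatment comparison of Dilapan-S (combined groups) versus Propess". It is a difference on the absolute scale.

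The covariates at issue are collected anyway. BMI is recorded at visit 1, where randomisation also takes place (Intervention description {11a}). Age is an eligibility criterion {10}, and date of birth is used to identify participants on the case report form (Confidentiality {27}). At visit 2, before insertion, "The cervix will be examined, and Bishop score will be determined". By then women have been told their group.

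**The concern.** The lower limit of one interval decides the trial. Outcome variation that baseline covariates could explain stays in that interval and widens it.

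The one adjusted analysis does not help with the decision as it is described. The ordinary output of a logistic regression is an odds ratio, and an odds ratio cannot be read against a margin of 10 percentage points. Unless it is converted to a risk difference, it can neither support nor challenge the non-inferiority conclusion.

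The leading population is per-protocol, with 15% non-adherence allowed for, and the Discussion reports that some randomised women never received the product. Exclusions after randomisation can create covariate imbalance, and a crude difference corrects none of it.

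**Working it through.** **Inputs.** From Sample size {14}: "SVD rates were assumed to be 70%, 75%, and 80% in the Propess, Dilapan-S® (24 h), and Dilapan-S® (12 h) groups, respectively", and "Assuming 90% statistical power, a one-sided 2.5% level of statistical significance, and equal treatment group allocation". The equal weights of the two Dilapan-S groups give a combined rate of (75% + 80%)/2 = 77.5%. The comparison with Propess is 2:1. The per-protocol size is 285, or 95 per group. The distance from the assumed difference to the margin is 0.775 − 0.70 + 0.10 = 0.175.

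**The plan's own figure.** Let n be the Propess group size.
- Variance term under the assumed rates: V1 = 0.70 × 0.30 + 0.775 × 0.225/2 = 0.2100 + 0.0872 = 0.2972.
- Farrington-Manning restricts the null rates to differ by exactly 10 points. The restricted estimates are 0.805 (Propess) and 0.705 (Dilapan-S), so V0 = 0.805 × 0.195 + 0.705 × 0.295/2 = 0.261.
- n = (1.960 × √0.261 + 1.2816 × √0.2972)² / 0.175² = 94.3, so 95 per group and 285 in total.

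The stated 285 is reproduced exactly for an unadjusted comparison.

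**Unadjusted precision at 285 (Wald).**
- SE = √(0.2972/95) = 0.0559.
- 95% half-width = 1.96 × 0.0559 = 10.96 points.
- Power = Φ(0.175/0.0559 − 1.96) = Φ(1.169) = 87.9%.

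**Effect of adjustment.** The documents do not say how prognostic age or BMI is, so this step rests on an assumption. Simulating the standardised risk difference at 285 with two covariates of log-odds 0.3 to 0.4 per SD or weaker gave an SE ratio, adjusted to crude, of 0.997 to 0.975, with no bias in the risk difference.

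| SE ratio | Half-width (points) | Wald power at 285 | Equivalent extra women, 285/ratio² − 285 |
|---|---|---|---|
| 1 (crude) | 10.96 | 87.9% | 0 |
| 0.997 | 10.93 | Φ(3.138 − 1.960) = 88.1% | 286.7 − 285 ≈ 2 |
| 0.975 | 10.69 | Φ(3.209 − 1.960) = 89.4% | 299.8 − 285 ≈ 15 |

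**Cross-check.** A second simulation used one composite covariate with log-odds 0.5 per SD. That matches two independent covariates of 0.3 and 0.4, since √(0.3² + 0.4²) = 0.5. Its variance ratio was 0.958, so the SE ratio was √0.958 = 0.979, close to the upper end above. With no prognostic value the variance ratio was 1.007, so a useless covariate costs almost nothing.

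**If 15% of 327 are lost.** 327 × 0.85 = 278. The crude SE is √(0.2972/92.65) = 0.0566 and power is 87.1%. With the same two ratios power becomes 87.3% to 88.7%.

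**The case against.** The strongest reply is that nothing here is wrong. A crude risk difference is valid, it is on the scale of the margin, and it is the comparison for which 285 was calculated. No stratification factor is named that the analysis would then have to include. All of this stands.

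Four stronger readings are tempting, and the documents do not support them.

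- **The trial is underpowered at 87.9%.** That figure comes from the Wald formula. Under Farrington-Manning, 285 delivers the stated 90%, and the article does not name its interval method. The Wald figures serve only to show the change.
- **Adjustment is worth some 32 women and 91% power.** That needs covariates explaining 10% of outcome variance: 285/0.90 − 285 ≈ 32. The two-covariate simulation does not reach it, and eligibility narrows the range of both age (18 to under 40) and BMI (below 35).
- **Bishop score is free precision too.** It is taken at visit 2 with allocation known, and it may be missing for women excluded before induction. It is not a clean baseline covariate for the primary model.
- **Adjustment repairs the per-protocol comparison.** It corrects imbalance in the measured covariates only. Selection on unmeasured factors is untouched, and no figure in the article shows that an imbalance has arisen.

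Two further objections stand in part. The article does not state an odds ratio, so the scale mismatch is an inference from an unstated effect measure, and the SAP may settle it. Also, changing the primary estimator late in an open-label trial with unblinded statisticians has a credibility cost, so the choice must be made without outcome data by arm. Neither shows a disadvantage of adjustment that is specified in advance. The low rank of adjustment is a choice the article itself makes and does not leave to the SAP.

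**Conclusion.** The point holds as a modest improvement in efficiency and not as an error or contradiction. The article fixes a crude primary estimate and ranks adjustment as exploratory, although two covariates held before randomisation could be used on the same 10-point scale.

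The gain is about 0.2 to 1.5 percentage points of Wald power at 285, or about 2 to 15 women. It rests on the protocol's assumed rates and on an assumed log-odds of 0.3 to 0.4 per SD or weaker for each covariate. If age and BMI predict almost nothing in this restricted population, the gain is near zero. Protection against imbalance from per-protocol exclusions is partial. I am confident about what the plan fixes and less so about the size of the gain.

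**What to change.** Before the SAP is finalised, which the Data management section places ahead of last-patient last-visit, and without reference to outcome data by arm:

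1. Define the primary estimate as the standardised (g-computation) risk difference from a logistic model with treatment, maternal age and visit-1 BMI. Give it a delta-method or robust 95% confidence interval and compare that with the 10-point margin.
2. Use the same estimator in the per-protocol and intention-to-treat populations.
3. Keep the crude difference in proportions as a supporting analysis.
4. Add the visit-2 Bishop score only in a named sensitivity analysis.
5. Record the date of the change and state that it was made without outcome data by arm.

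The cost is protocol and SAP wording and a few lines of code. No extra data, visits or participants are needed, and the margin and sample size do not change.
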